## Rescue medication

The subjects are allowed to take the following rescue medications if pain control is difficult with the investigational products:

 Acetaminophen (Hanmi Susphen ER 650 mg tablet); a maximum of 3 g / day and 30 - 50 tablets per person.

For the above drug, the amount and duration used should be recorded on a case report form.

 Administration criteria for the rescue medication:

Subjects who experience an unacceptable degree of pain during the study period can be given acetaminophen 650 mg for additional pain control. For this, subjects must be given the appropriate amount of rescue medication after randomization. Subjects must be educated not to take more than 3 g / day of acetaminophen 650 mg. The amount of rescue medication used should be recorded in the subject file, and the remaining amount must be returned at the end of the study to confirm the total amount used. The above information must be given to the subjects by the investigator.

## Drugs or therapies contraindicated prior to study participation

Subjects who received the following medications for the periods listed below cannot participate in the study:

1. NSAIDs (LDA [≤325 mg / day low dose aspirin] excluded) within 7 days prior to administration of the investigational product.
2. Gastroprotective agents (including H2 blockers, PPIs, misoprostol, etc.) within 7 days prior to administration of the investigational product.
3. IV or oral corticosteroids (oral corticosteroids corresponding to ≤7.5 mg / day prednisone, topical ointments, eyedrops, and nasal agents are excluded) within 7 days prior to investigational product administration.
4. Intraarticular or intramuscular corticosteroids or hyaluronic acid within 8 weeks prior to administration of the investigational product.
5. Glucosamine and / or chondroitin sulfate within 7 days prior to administration of the investigational product.
6. Lithium within 7 days prior to administration of the investigational product.
7. Antiretrovirals (atazanavir, atazanavir sulfate) within 7 days prior to administration of the investigational product.

## Drugs or therapies contraindicated during study participation

Drugs other than investigational products, especially one of the drugs listed below, should not be administered during the study period, on principle:

1. NSAIDs (LDA [<325 mg/day low dose aspirin] excluded) other than investigational products.
2. Other gastroprotective drugs (H2 blockers, PPIs, misoprostol, etc.).
3. IV or oral corticosteroids (oral corticosteroids corresponding to ≤7.5 mg / day prednisone, topical ointments, eyedrops, nasal agents excluded).
4. Intraarticular or intramuscular corticosteroids or hyaluronic acid.
5. Glucosamine and / or chondroitin sulfate.
6. Lithium.
7. Antiretrovirals (atazanavir, atazanavir sulfate).

All drugs deemed necessary by the investigator, as per the investigator’s medical opinion, can be given. However, if a drug administered without an investigator’s assessment is deemed to have the capacity to influence the safety and efficacy evaluation of this study, the corresponding subject will be excluded from PP analysis. All drugs administered, and their dosage, route of administration, and reason for administration, must be recorded in a case report form signed by the investigator.

## Precautions regarding the experimental drug

## Adverse events associated with the experimental drug

1. A comparison of the safety data for this drug and of that for each of naproxen and esomeprazole, the active ingredients in this drug, indicated that there was no novel safety information.
2. Adverse events associated with this drug in a clinical study have been classified as shown below, according to frequency and System Organ Class (SOC). Frequency is defined as follows: very common (>1/10), common (>1/100, <1/10), uncommon (>1/1,000, <1/100), rare (>1/10,000, <1/1,000), very rare (<1/10,000), and unknown (cannot be measured in usable data).

|  | Very common | Common | Uncommon | Rare |
| --- | --- | --- | --- | --- |
| Infection |  |  | Infection | Diverticulitis |
| Hematological or lymphatic disorder |  |  |  | Eosinophilia, leukopenia |
| Immune disorder |  |  |  | Hypersensitivity |
| Metabolic and nutritional disorder |  |  | Decreased appetite | Fluid retention, hyperkalemia, hyperuricemia |
| Psychiatric disorder |  |  | Anxiety, depression, insomnia | Confusion, abnormal dreams |
| Neurological disorder |  | Dizziness, headache, dysgeusia | Cognitive disorder, syncope | Somnolence, tremor |
| Ear and labyrinth disorder |  |  | Tinnitus, vertigo |  |
| Cardiovascular disorder |  |  | Arrhythmia, tachycardia | Myocardial infarction, tachycardia |
| Vascular disorder |  | Hypertension |  |  |
| Respiratory, chest, and mediastinal disorder |  |  | Asthma, bronchospasm, dyspnea |  |
| Gastrointestinal disorder | Dyspepsia | Abdominal pain, constipation, diarrhea, esophagitis, flatulence, gastroduodenal ulcer*, gastritis, nausea, vomiting | Gastrointestinal bleeding, oral mucositis | Glossitis, hematemesis, rectal bleeding |
| Skin and subcutaneous tissue disorder |  | Rash | Dermatitis, hyperhidrosis, pruritis, hives | Alopecia, ecchymosis |
| Musculoskeletal and connective tissue disorder |  | Arthralgia | Myalgia |  |
| Renal and urological disorder |  |  |  | Proteinuria, renal failure |
| Reproductive and breast disorder |  |  |  | Menstrual disorder |
| Systemic disorder |  | Edema | Lethargy, tiredness, fever |  |
| Laboratory disorder |  |  | Abnormal liver function, elevated serum creatinine |  |

*: Confirmed by planned general gastroscopy.

1. Adverse events shown in clinical and post-marketing studies of naproxen are as follows:
2. Hypersensitivity: symptoms of shock (dyspnea, hypotension, bradycardia, diaphoresis, edema, etc), PIE syndrome (pulmonary infiltration with eosinophilia: fever, wheeze, cough, sputum), anaphylactic reaction, hives, rash, and pruritis.
3. Gastrointestinal: hematemesis, peptic ulcers, perforation, gastric discomfort, gastric pain, abdominal pain, nausea, vomiting, decreased appetite, dyspepsia, heartburn, diarrhea, constipation, stomatitis, distension, malena, thirst, esophagitis, gastritis, glossitis, belching, flatulence, coffee-ground vomit, pancreatitis, colitis, exacerbation of inflammatory bowel disease (ulcerative colitis, Crohn’s disease), and ulcerative stomatitis.
4. Hematological: agranulocytosis, neutrophilia, granulocytopenia, pancytopenia, leukopenia, thrombocytopenia, aplastic anemia, hemolytic anemia, platelet dysfunction (prolongation of the bleeding time), and lymphadenitis.
5. Hepatic: GOT and GPT elevation, jaundice, hepatitis, liver failure, and cholestatis.
6. Renal: renal dysfunction, glomerular nephritis, hematuria, interstitial nephritis, renal syndrome, renal papillary necrosis, proteinuria, renal failure, and oliguria / polyuria.
7. Central nervous system:

- Somnolence and cognitive dysfunction; rarely dizziness, headache, paresthesia, decreased libido, fatigue, depression, dream abnormalities, inability to concentrate, disorientation, insomnia, myalgia, muscle weakness, agitation, anxiety, confusion, hallucination, nervousness, lethargy, and myasthenia gravis.

- Aseptic meningitis (discontinue the drug and consult physicians if the following symptoms occur: severe headache, nausea, vomiting, neck stiffness, fever, and / or an altered level of consciousness).

1. Respiratory: dyspnea, asthma, bronchospasm, eosinophilic pneumonitis, pneumonia, pulmonary edema, and decreased respiration.
2. Dermatological: pruritis, ecchymosis, rash, eczema, sweating, purpura, photosensitivity, alopecia, redness, toxic epidermal necrolysis (TEN), erythema multiforme, erythema nodosum, fixed drug eruption, lichen sclerosis, porphyria cutanea tarda, exfoliative dermatitis, and bullous skin reaction.
3. Sensory: tinnitus, hearing disorder, and vision disorder.
4. Metabolic and nutritional: edema, fluid retention, hyperglycemia, hypoglycemia, hyperkalemia, and hyperuricemia.
5. Infection: diverticulitis, infection, and sepsis.
6. Other: angioneurotic edema, palpitations, congestive heart failure, infertility, menstrual disorder, chills, fever, vasculitis, and serum creatinine elevation.
7. Adverse events shown in clinical and post-marketing studies of enteric coated esomeprazole are as follows (no dose relationship was seen):

|  | Common | Uncommon | Rare | Very rare | Not known |
| --- | --- | --- | --- | --- | --- |
| Blood and lymphatic system disorders |  |  | Leukopenia, thrombocytopenia | Agranulocytosis, pancytopenia |  |
| Immune system disorders |  |  | Hypersensitivity reactions e.g. fever, angioedema and anaphylactic reaction/shock |  |  |
| Metabolism and nutritional disorders |  | Peripheral edema | Hyponatremia | Hypomagnesemia |  |
| Psychiatric disorders |  | Insomnia | Agitation, confusion, depression | Aggression, hallucinations |  |
| Nervous system disorders | Headache | Dizziness, paresthesia, somnolence | Taste disturbance |  |  |
| Eye disorders |  |  | Blurred vision |  |  |
| Ear and labyrinths disorder |  | Vertigo |  |  |  |
| Respiratory, thoracic, and mediastinal disorders |  |  | Bronchospasm |  |  |
| Gastrointestinal disorders | Abdominal pain, diarrhea, flatulence, nausea / vomiting, constipation | Dry mouth | Stomatitis, gastrointestinal candidiasis | Microscopic colitis | *C. difficile* diarrhea |
| Hepatobiliary disorders |  | Increased liver enzymes | Hepatitis with or without jaundice | Hepatic failure, hepatic encephalopathy in patients with preexisting liver disease |  |
| Skin and subcutaneous tissue disorders |  | Dermatitis, pruritus, urticaria, rash | Alopecia, photosensitivity | Erythema multiforme, Stevens-Johnson syndrome, toxic epidermal necrolysis (TEN) (partially fatal) |  |
| Musculoskeletal and connective tissue disorders |  |  | Arthralgia, myalgia | Muscular weakness |  |
| Renal and urinary disorders |  |  |  | Interstitial nephritis |  |
| Reproductive and breast disorders |  |  |  | Gynecomastia |  |
| General and administration site disorders |  |  | Malaise, increased sweating |  |  |

## Contraindications for the experimental drug

The following are contraindications for this drug:

1. Known hypersensitivity to naproxen, esomeprazole, any component of this drug, or substituted benzimidazoles.
2. A history of asthma, rhinitis, nasal polyps, urticaria, or other allergic-type reactions after taking aspirin or other NSAIDs, including COX-2 inhibitors (fatal and severe anaphylactic reaction has rarely been reported in such patients after NSAID use).
3. Active peptic ulcer disease.
4. Gastrointestinal bleeding, cerebrovascular bleeding, other bleeding disorders, or a severe hematological disorder.
5. Severe hepatic dysfunction (e.g. Child-Pugh class C).
6. Severe cardiac failure.
7. Severe renal failure (CrCl <30 mL / min).
8. Severe hypertension.
9. Use during the peri-operative period of coronary artery bypass graft (CABG) surgery.
10. Use during the last 3 months of pregnancy.
11. Atazanavir or nelfinavir use.

## Warnings for use of the experimental drug

Warnings for use of the experimental drug are as follows:

1. If a patient who regularly drinks 3 or more standard drinks / day requires this drug or another antipyretic analgesic agent, a physician or pharmacist must be consulted. Such a person may be at an increased risk of gastrointestinal bleeding.
2. Cardiovascular risk: Use of NSAIDs, including this drug, may increase the risk of major cardiovascular events, myocardial infarction, and stroke, all of which can be fatal. This risk can increase with increasing duration of administration, and may be increased in patients with pre-existing cardiovascular disease or risk factors. The physician and patient must both carefully monitor for symptoms of such cardiovascular events, even without a history of cardiovascular disease. The patient must be aware of signs and / or symptoms of major cardiovascular toxicity and the appropriate response to take should such symptoms occur.
3. Gastrointestinal risk: Use of NSAIDs, including this drug, can increase the risk of gastrointestinal adverse events, including gastrointestinal bleeding, ulcers, or perforation, all of which can be fatal. This drug significantly reduced the incidence of GI ulcers compared to naproxen alone, but ulcers and their complications may still occur. Such adverse events can occur without warning symptoms during treatment. Elderly patients may be at an increased risk of such serious GI adverse events. A longer duration of treatment can increase the risk of GI adverse events, but short-term administration does not rule out such risks. Patients must be carefully monitored for signs or symptoms of GI ulcers or bleeding while on this drug. If serious GI adverse events are suspected, immediately perform additional assessments and provide treatment. It may be necessary to discontinue NSAID use until there is a complete resolution of serious GI adverse events. In high-risk groups, alternative treatments that are not related to NSAIDs should be considered.

## Precautions for the use of the experimental drug

#### Administration with caution

Administer cautiously to:

1. Patients with a history of peptic ulcers.
2. Patients with hematological disorders or a history of hematological disorders.
3. Patients with bleeding diathesis (which may decrease platelet function).
4. Patients with liver dysfunction or a history of liver dysfunction.
5. Patients with renal dysfunction, a history of renal dysfunction, or decreased renal blood flow.
6. Patients with cardiac dysfunction.
7. Patients with hypertension.
8. Patients with hypersensitivity.
9. Patients with bronchogenic asthma.
10. Patients with induced porphyria, systemic lupus erythematosus (SLE), or mixed connective tissue disease (MCTD).
11. Elderly patients.

#### General precautions

1. Carefully consider the potential benefits and risks of this drug and other treatment options before deciding to use this drug. When administering this drug, adequately monitor progress and use the lowest effective dose for an appropriate amount of time.
2. It must be noted that NSAID therapy is a symptomatic, rather than a curative, treatment.
3. Long-term (especially 1 year or longer) therapy with this drug must be monitored regularly by clinical tests (urine analysis, complete blood count, chemistry profile, liver function test, eye test, etc.). If abnormalities are noted, appropriate management, including dose reduction or temporary discontinuation, must be implemented. If clinical signs and / or systemic manifestations (e.g. eosinophilia, rash, etc.) consistent with liver disease or renal disease develop, or abnormal liver function tests or renal function tests persist or worsen, this drug should be discontinued.
4. Patients must be monitored sufficiently for any adverse events. Excessive hypothermia, lethargy, or cool periphery can occur. Therefore, the patient’s condition must be carefully noted, especially in elderly patients or patients with a wasting disease. Debilitated patients should be given the lowest dose possible and monitored for incidence of adverse events.
5. Based on the pharmacological properties of this drug, any signs and symptoms of fever or inflammation may be muted, delaying the diagnosis of infectious complication under conditions of pain or non-infection.
6. Gastrointestinal effects:
7. NSAIDs should be prescribed with extreme caution in patients with a prior history of ulcerative disease or gastrointestinal bleeding. Patients with a prior history of peptic ulcers and / or gastrointestinal bleeding who use NSAIDs have a greater than 10-fold increased risk of developing a GI bleed than patients with neither of these risk factors. Other factors that increase the risk of GI bleeding in patients treated with NSAIDs include concomitant use of oral corticosteroids or anticoagulants, a longer duration of NSAID therapy, smoking, use of alcohol, older age, and poor general health status. Most spontaneous reports of fatal GI events are in elderly or debilitated patients and therefore special care should be taken in treating this population. Co-administration with misoprostol or a proton pump inhibitor must be considered in such patients.
8. If GI bleeding or ulcers occur during administration of this drug, this drug must be discontinued.
9. NSAIDs should be given with care to patients with a history of gastrointestinal disease (ulcerative colitis or Crohn's disease) as these conditions may be exacerbated.
10. In the presence of any alarm symptom (e.g. significant unintentional weight loss, recurrent vomiting, dysphagia, hematemesis or melaena) and when a gastric ulcer is suspected or present, malignancy should be excluded as treatment with esomeprazole magnesium may alleviate symptoms and delay diagnosis.
11. Treatment with proton pump inhibitors may slightly increase the risk of gastrointestinal infections such as *Salmonella* and *Campylobacter.*
12. Esomeprazole might reduce the absorption of vitamin B12 (cyanocobalamin) due to hypo- or achlorhydria. This should be considered in patients on long-term therapy with a risk of reduced vitamin B12 absorption or storage.

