## Study withdrawal

A subject can withdraw from the study at any time and is not obliged to reveal the reason. A subject must be withdrawn from the study if one of the situations below arises:

- - Withdrawal of consent by the subject or the subject’s legal proxy.
  - The investigator’s assessment that continued participation in the study is harmful to the subject.
  - Adverse events too serious to continue the study (CTCAE grade 4 or 5) or difficulty with study participation as per the investigator’s assessment.
  - Serious protocol violation as per the sponsor or investigator’s assessment.
  - Unfit to continue in the study as per the sponsor or investigator’s assessment.
  - A subject’s wish to withdraw from the study for other reasons.

In cases of serious protocol violation as listed below, the corresponding subject must be excluded from the analysis (PP excepted):

- - Need for cessation of study participation due to the possibility of biasing the efficacy or safety evaluation of the experimental drug, or the violation of inclusion / exclusion criteria that can affect the safety of a subject, as per the investigator or sponsor’s assessment.
  - Notification by a subject of the use of another drug or treatment for the study’s target disease during the study period, and the investigator’s conclusion that the subject has no intention of ceasing the use of such drug or treatment.
  - The use or administration of drugs contraindicated for co-administration with the investigational product, as stated in Section [5.3.3](#_bookmark68).
  - Subjects who did not undergo washout for specified drugs before randomization.
  - Incorrect randomization.
  - Less than 80% compliance rate.

If the follow-up of a withdrawn subject is not possible, the investigator must make an effort to confirm the address and health status of subject. If a subject is withdrawn from the study, all efforts must be made to record, in full detail, the reason and situation leading to their withdrawal. If a subject withdraws early, the evaluation and treatment corresponding to Visit 3 must be conducted, when possible in addition to an appropriate assessment to determine the reason for early withdrawal, including any adverse reactions to the investigational products (refer to Section 6.1). The reason for withdrawal must be recorded in case report form for all cases.

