## Discontinuation of investigational product use

Administration of the investigational product must be discontinued if any of the below situations arise during the study:

- - Fulfillment of exclusion criteria that can affect the safety of a subject and necessitate discontinuation of the investigational product administration, as per the clinical assessment by the investigator or sponsor.
  - Adverse events for which temporary or permanent discontinuation of the investigational products is necessary, as per the assessment of the investigator or subject.
  - Administration of drugs contraindicated for co-administration that require discontinuation of the investigational products, as stated in Section 5.3.3.
  - Serious non-compliance to administration of the investigational product.

The investigator must ensure that the administration of the investigational products is as planned. If investigational product use is discontinued by a subject, all observations necessary and possible must be made and recorded, as in the case of study withdrawal. In all cases of discontinuation of the investigational product, the reason, situation, and duration must be recorded in case report form.

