# Investigational product and other study drugs

“Investigational medicinal product” includes the experimental drug and the control drug.

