## Contraindications for the control drug

1. Patients with hypersensitivity or a history of hypersensitivity to this drug or its components.
2. Patients with an allergic reaction to sulfonamides.
3. Patients with a history of asthma, acute rhinitis, nasal polyps, angioedema, urticaria, or allergic reaction to aspirin or other NSAIDs (including COX-2 inhibitors).
4. Patients with severe hepatic impairment.
5. Patients with severe renal impairment (CrCl <30 mL / min).
6. Patients with active peptic ulcer disease or GI bleeding.
7. Patients with inflammatory bowel disease, such as Crohn’s disease or ulcerative colitis.
8. Patients with congestive heart failure (NYHA II-IV).
9. Patients with confirmed ischemic heart disease, peripheral arterial disease, and / or cerebrovascular disease.
10. Pregnant women, or women of childbearing age.
11. Lactating women.
12. Patients being treated for post-carotid arterial bypass graft (CABG) pain.
13. Patients with hyperkalemia.
14. This drug contains lactose. Therefore, patients with genetic conditions such as galactose intolerance, Lapp lactase deficiency, or glucose-galactose malabsorption should not be given this drug.

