## Warnings for the use of the control drug

Warnings for use of the control drug are as follows:

1. If a person who regularly drinks more than 3 standard drinks per day requires this drug or another antipyretic analgesic drug, a physician or a pharmacist must be consulted. Such a person is at an increased risk of gastrointestinal bleeding.
2. Cardiovascular risk: NSAIDs, including this drug, may cause an increased risk of serious adverse cardiovascular thrombotic events, myocardial infarction, and stroke, all of which can be fatal. This risk may be increased with increasing duration of treatment, and may be higher in patients with cardiovascular disease or cardiovascular risk factors. Physicians and patients should remain alert for the development of such events, even in the absence of previous cardiovascular symptoms. Patients should be informed about the signs and / or symptoms of serious cardiovascular toxicity and the steps to take if they occur.
3. Gastrointestinal risk: NSAIDs, including this drug, can cause serious gastrointestinal adverse events including bleeding, ulceration, and perforation of the stomach, small intestine or large intestine, all of which can be fatal. Although this drug significantly reduced the risk of peptic ulcers compared to naproxen alone, adverse events, including ulceration and related complications, still occur. These events can occur at any time, with or without warning symptoms, during treatment with NSAIDs. The risk of serious gastrointestinal adverse events may be higher in the elderly. A longer duration of treatment may increase the risk of serious gastrointestinal adverse events, but a shorter treatment duration does not exempt patients from this risk. Patients must be carefully monitored for signs and symptoms of gastrointestinal ulcers or bleeding. If serious gastrointestinal adverse events are suspected, additional evaluation and treatment must be immediately given. It may be necessary to discontinue NSAID therapy until all serious gastrointestinal adverse events have been ruled out. In high risk groups, an alternative, non-NSAID therapy must be considered.

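### The protocol gives inconsistent instructions on study drug when GI bleeding or ulcer occurs, and a blinded investigator cannot tell which applies

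*Protocol*

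**What the plan says.** Seven places in the protocol bear on what happens to study drug after GI bleeding or ulcer.

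- **Section 5.3.4.4, General precautions (experimental drug):** "If GI bleeding or ulcers occur during administration of this drug, this drug must be discontinued". No grade, judgement or duration is attached.
- **Section 5.3.4.3, Warnings (experimental drug):** once serious GI events are suspected, "It may be necessary to discontinue NSAID use until there is a complete resolution of serious GI adverse events".
- **Section 5.3.5.3, Warnings (control drug):** in the same setting, "It may be necessary to discontinue NSAID therapy until all serious gastrointestinal adverse events have been ruled out". The control-drug sections have no sentence that requires celecoxib to be stopped when GI bleeding or ulcer occurs.
- **Section 5.3.4.2, Contraindications (experimental drug):** "Gastrointestinal bleeding, cerebrovascular bleeding, other bleeding disorders, or a severe hematological disorder", with active peptic ulcer disease as a separate item.
- **Section 5.3.5.2, Contraindications (control drug):** "Patients with active peptic ulcer disease or GI bleeding".
- **Section 4.5.2, Discontinuation of investigational product use:** the list of triggers includes "Adverse events for which temporary or permanent discontinuation of the investigational products is necessary, as per the assessment of the investigator or subject". Another bullet covers exclusion criteria that bear on safety, subject to clinical assessment by the investigator or sponsor. Section 5 says that the investigational product "includes the experimental drug and the control drug", so this is one rule for both arms.
- **Section 4.5.1, Study withdrawal:** withdrawal follows adverse events of CTCAE grade 4 or 5, or the investigator's assessment that participation is difficult.

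Section 4.1 sends the reader to Sections 5.3 and 5.4 for warnings. No section says which text governs when they differ.

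**The concern.** The same event leads to different instructions depending on the section consulted: a stop without qualification, a possible stop on suspicion, or a decision by assessment. The unqualified instruction belongs to one product only. Under double-blinding (Section 5.8) the investigator does not know which product the subject is taking, and so cannot know whether that instruction is in force.

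The product warnings describe these events as potentially fatal. The trial has no data safety monitoring committee (Section 1.4) and no scheduled visit between Day 1 and about Day 84 (Section 6.1). Decisions will therefore be taken at unscheduled contacts across 10 sites, where a single clear instruction matters most. Product-specific wording could also prompt unblinding that one common rule would make unnecessary.

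There is a lesser statistical link. Discontinuation due to GI adverse events is a secondary endpoint compared between arms (Sections 7.3.2 and 7.5.3), and inconsistent stopping would add site-dependent noise to it.

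**Working it through.** **Step 1: compare the texts by trigger and action.**

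- Precautions, experimental drug: the trigger is occurrence; the action is required.
- Warnings, experimental drug: the trigger is suspicion of a serious event; the action is possible and lasts until resolution.
- Warnings, control drug: the trigger is suspicion of a serious event; the action is possible and lasts until the event is excluded.
- Section 4.5.2, adverse-event bullet: the trigger is any adverse event judged to need it; the action is temporary or permanent. GI bleeding and ulcer are not named.
- Section 4.5.2, exclusion-criteria bullet: this reaches both conditions, because exclusion items 5 and 12 in Section 4.3.2 cover active peptic ulcer disease and GI bleeding, but again only by clinical judgement.
- Contraindications, both drugs: both conditions are listed, with no statement about onset during treatment.
- Section 4.5.1: this concerns leaving the study, by grade 4 or 5 or by assessment.

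The precaution and Section 4.5.2 cannot both be followed literally when an investigator judges that stopping is not needed. The two experimental-drug texts also fit poorly together: a possible stop lasting until resolution presupposes that an event has occurred, which is where the precaution requires a stop.

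**Step 2: the denominator.** Section 7.1 uses a standard deviation of 0.65, a margin of 0.40, one-sided alpha 0.025 and 80% power: 2 × 0.65² × (1.96 + 0.842)² / 0.40² = 41.46, rounded up to 42. With 20% drop-out, 42 / 0.80 = 52.5, rounded up to 53 per arm. The plan's figure is reproduced. None of its inputs depends on the stopping text.

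**Step 3: expected events.** Section 5.3.4.1 classes gastroduodenal ulcer as common (1/100 to 1/10) and GI bleeding as uncommon (1/1,000 to 1/100) for the experimental drug. Assume that these frequencies apply over 12 weeks:

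- Bleeding: 53 × 0.001 = 0.05 to 53 × 0.01 = 0.53.
- Ulcer: 53 × 0.01 = 0.53 to 53 × 0.10 = 5.3.

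The ulcer class was confirmed by planned gastroscopy, which this trial does not schedule, so its upper end is probably too high here. For celecoxib, the Korean post-marketing figure of 2 gastric ulcers in 5,648 (Section 5.3.5.1) gives 53 × 2 / 5,648 = 0.02.

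About 0 to 6 experimental subjects could therefore be counted as discontinued or not, according to the text followed.

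**Step 4: what that could do to the secondary endpoint.** Fisher's exact two-sided p with 53 per arm:

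- 4 versus 0: 0.118
- 5 versus 0: 0.057
- 6 versus 0: 0.027

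Only the extreme upper end, with every case in one arm and none in the other, would cross 0.05.

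**The case against.** The strongest reply is that Sections 5.3.4 and 5.3.5 are general product information. The nearby control-drug text gives doses for other indications, and the experimental-drug precautions discuss therapy of a year or longer. On this view the trial's own rules are in Section 4.5, are the same for both arms, and already reach both conditions through the exclusion criteria. The warnings act on suspicion and the precaution on occurrence, so discretion first and a stop later can be read as compatible. Emergency unblinding is available under Section 5.9.

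Part of this stands. The difference in triggers softens the conflict, especially with the control-drug warning. Section 4.5.2 is not silent on these conditions, although it reaches them only by judgement. The argument from product information does not settle the matter: Section 4.1 directs investigators to Section 5.3 for warnings, the precaution is worded as an instruction, and nothing says that Section 4.5.2 overrides it.

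A reader might infer more than the documents support:

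- **A separate stopping rule for each arm.** The experimental-drug warnings are conditional too, both conditions are contraindications for both drugs, and Section 4.5.2 is common to both arms. The contrast between arms rests on one sentence.
- **A permanent stop under the precaution.** It does not give a duration.
- **A bias between arms in the discontinuation endpoint.** That would need investigators to guess the arm or unblind and then act on that product's text, which nothing in the protocol shows.
- **A contrast between everyone stopping and no one stopping.** This describes who is compelled to stop under each text. It is not an expected effect, because judgement would often lead to stopping.

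**Conclusion.** The inconsistency is real and should be reconciled. It lies between the mandatory precaution for the experimental drug, the conditional warnings for both drugs, and the assessment-based rule in Section 4.5.2. Because the mandatory sentence is tied to one product, a blinded investigator cannot tell whether it applies, and sites may act differently.

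The consequence is mainly for subject safety and consistency between sites. The effect on discontinuation due to GI adverse events is likely small. The expected counts rest on the assumption that label frequencies carry over to 12 weeks, and the upper ulcer figure on endoscopic detection that this trial does not plan. It is also uncertain how far these events enter the endpoint: the five symptoms listed for GI adverse event incidence in Section 7.3.2 include neither bleeding nor ulcer, and the discontinuation endpoint has no list. The primary LDQ analysis and the sample size are unaffected.

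**What to change.** Reconcile Sections 4.5.1, 4.5.2, 5.3.4.2, 5.3.4.3, 5.3.4.4 (General precautions), 5.3.5.2 and 5.3.5.3. Put one arm-independent statement in Section 4.5.2 saying what happens to study drug when GI bleeding or ulcer is suspected and when it is confirmed, in terms that can be applied without knowing the allocation. Have both product sections refer to that statement and say that it governs during the trial. The clinical content is for the sponsor and investigators to decide.

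The cost is a change of protocol wording, handled under Section 9.5, and a memo to sites. It needs no new data, visits or subjects.
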